## Methods/design

### Main objective

The main objective of the study is to evaluate the efficacy in functional capacity, lifestyle indicators and psychological wellbeing of a new CR program with MI carried out entirely in primary healthcare in patients discharged from hospital after AMI.

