### Sample size calculation

The six-minute walk test is sensitive and specific in measuring changes in functional capacity. Evidence shows the minimum clinically-relevant difference is 30 m [31, 32]. Accepting an alpha risk of 0.05 and a beta risk of 0.2 in a bilateral contrast, with a standard deviation of 80 m in the six-minute walk test, 284 participants (142 in the intervention group and 142 in the control group) will be required to detect differences of ≥ 30 m. To achieve adequate participant enrollment and reach the minimum sample size, we analyzed the incidence of new AMI in the six PHC areas and foresee that three years will be sufficient to reach the minimum sample size.

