### Statistical methods

Outcomes will be evaluated at 1, 3 and 6 months. Participant characteristics will be described using central tendency measures: mean or median and variability: standard deviation or interquartile range for continuous variables, and frequencies and percentages for categorical variables. The results of the physical functional capacity and the six-minute walk test will be transformed into units of metabolic equivalent of task (MET) using the equation and conversion table of the American College of Sports Medicine [33]. Between-group differences will be studied using the Student’s t-test for two samples. The magnitude of the effect will be calculated using Cohen's D. The effect of the intervention or standard care will be calculated using the Student’s t-test or Mcnemar’s test for paired samples. A mixed linear regression model will be used to evaluate trends in each arm, adjusting for variables of interest. For the inference analysis, co-variables that correlate (sociodemographic factors) will be used and adjusted analyzes made. In the comparison of multiple hypotheses, adjustment of the level of statistical significance (α = 0.05) will be used to avoid type I errors. All analyzes will made per protocol and intention-to-treat. The analysis will be made using R v3.5.2 [34].

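### No deciding time point is fixed for the six-minute walk test, and the alpha adjustment has no stated scope, so the 80% power depends on how the plan is read

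*Protocol article*

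**What the plan says.** **Sample size calculation.** One test is assumed: "Accepting an alpha risk of 0.05 and a beta risk of 0.2 in a bilateral contrast". The SD is put at 80 m and the difference to detect at 30 m. The result is 284 participants, "142 in the intervention group and 142 in the control group". No time point, multiplicity allowance or dropout rate is given.

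**Main outcome.** This is improvement on the six-minute walk test, with no time point or contrast.

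**Timing.** Statistical methods says "Outcomes will be evaluated at 1, 3 and 6 months", and the Abstract gives the same three times. Table 2 has two marks in the walk-test row, read here as visit 4 (week 4) and visit 10 (week 23). It has none at 3 months and none at the first data-collection visit.

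**Multiplicity.** Statistical methods says "In the comparison of multiple hypotheses, adjustment of the level of statistical significance" will be used, starting from 0.05. Neither the hypotheses in the family nor the method is named. The same section plans both per-protocol and intention-to-treat analyses and ranks neither.

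**Scope and scale.** The Main objective is to "evaluate the efficacy in functional capacity, lifestyle indicators and psychological wellbeing". Statistical methods converts the walk result to METs, whereas the sample size is in metres ("the minimum clinically-relevant difference is 30 m").

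**The concern.** A sample size has a meaning only for a defined test at a defined alpha. Here the design section assumes one test at the full 0.05. The analysis section allows for more than one and says that alpha will be adjusted where several hypotheses are compared.

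If the walk test is read at each scheduled visit and alpha is not adjusted, the error rate on the main outcome exceeds 5%. If alpha is adjusted across those visits, the sample size has made no provision for it.

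The reading of the result is also open. Table 1 places the four scheduled interview sessions at 72 hours and weeks 2, 5 and 8. A week-4 walk test therefore follows only two of the four. As written, a difference at week 4 that is gone by week 23 could be reported as success on the main outcome, and so could the reverse pattern.

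**Working it through.** **Inputs.** From Sample size calculation: difference 30 m, SD 80 m, two-sided alpha 0.05, power 80%, 142 per arm. The standardised difference is 30/80 = 0.375. Assumed, because the document is silent: Bonferroni as the adjustment, 10% or 20% loss, and a correlation of 0.5 to 0.8 between walk tests in the same patient.

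**Step 1: the plan's own figure.** The normal approximation is n per arm = 2 × (z for 1−α/2 + z for power)² / 0.375² = 2 × (1.960 + 0.842)² / 0.1406 = 111.7, so 112. The t-test gives 112.6, so 113 per arm (226 in total). This is not 142 per arm (284). The figure of 142 would follow from 113 with about 20% loss (113/0.80 = 141.25, rounded up to 142), but no such allowance is stated. The results below are therefore shown first at 142 evaluable per arm, then with loss.

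**Step 2: power if alpha is split.** Power comes from the two-sample t-test with non-centrality 0.375 × √(n/2). For n = 142 this is 0.375 × √71 = 3.16. A 10% loss leaves 142 × 0.9 = 127.8, taken as 128. A 20% loss leaves 142 × 0.8 = 113.6, taken as 113.

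| Evaluable per arm | One test, α = 0.05 | Two tests, α = 0.025 | Three tests, α = 0.0167 |
|---|---|---|---|
| 142 (no loss) | 88.3% | 81.7% | 77.3% |
| 128 (10% loss, assumed) | 84.8% | 77.1% | 72.2% |
| 113 (20% loss, assumed) | 80.1% | 71.3% | 65.8% |

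Two tests match Table 2. Three tests match the text.

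**Step 3: where 80% is crossed.** With two tests, 80% power needs 136.4, so 137 per arm. That tolerates a loss of 1 − 137/142 = 3.5%. With three tests it needs 150.3, so 151 per arm, which is more than the 142 planned.

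**Step 4: error rate if alpha is not split.** For two standard normal statistics with correlation r, each tested at |z| > 1.96, the probability of at least one rejection under no effect is 9.1% (r = 0.5), 8.3% (r = 0.7) and 7.8% (r = 0.8).

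**The case against.** The strongest reply is that the plan names one main outcome, gives it the full 0.05, and means the adjustment for the many other measures. On that reading the primary power is untouched. The details of the adjustment may also sit in an analysis plan that is not shown. This is a fair reading and nothing rules it out. The method of adjustment can indeed wait. The conflict between three evaluation times and two scheduled walk tests, and a sample size with no time point, are in the protocol itself.

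It may also be said that improvement with two walk tests implies a single contrast, the change from week 4 to week 23. That is possible but not stated. It would also measure change from a point at which the intervention is already under way.

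Three stronger readings may tempt a reader, and the document does not support them:

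- **That the 80% power is lost.** With all 284 evaluable, one test has 88% power and two Bonferroni tests have 82%. Figures near 71% or 66% need an assumed loss of about 20%.
- **That metres versus METs is a second hypothesis that costs alpha.** Table 4 names distance as the outcome and treats METs as a conversion. What remains is that a result shown only in METs cannot be set against the 30 m threshold.
- **That the three-domain objective creates three primary tests.** The Main outcome section names the walk test alone. The objective is loosely worded, but it does not divide alpha.

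**Conclusion.** The point holds in a limited form. The protocol does not fix which walk test decides the trial. Its text and Table 2 disagree on how many there are, and it does not say whether the alpha adjustment reaches the main outcome.

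Power for 30 m therefore runs from 88% (one test, no loss) to 66% (three tests, assumed 20% loss). The reading closest to Table 2, two tests with no loss, gives 82%, and it falls below 80% once loss exceeds about 3.5%. Without adjustment, two tests carry an error rate of about 8-9%.

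These figures rest on the stated 30 m and 80 m, on Bonferroni, and on the assumed losses and correlations. They also rest on reading Table 2 from extracted text. The fault is one that should be corrected, and it does not show that the trial is too small.

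**What to change.** Reconcile the three evaluation times in the text with the two walk-test marks in Table 2. Then state in the protocol:

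- **Primary test:** the between-arm difference in six-minute walk distance, in metres, at the 6-month (week-23) assessment, two-sided alpha 0.05, by intention to treat.
- **Secondary:** the week-4 walk test and all other outcomes, with the multiplicity adjustment applied among them.
- **METs:** a supportive re-expression of the same measurement.

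This restores the single test that the sample size assumes. It should be made before any outcome data are seen by arm. It needs a wording change and no extra patients. The cost is that an effect present only at 1 month cannot be claimed as the primary result.

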### Strategies to improve adherence to the protocol

To maximize adherence, study collaborators will send reminders of data collection sessions and visits by phone. If patients do not attend, they will be contacted again to avoid losses. Sessions will take place at the initial product dispensing and each study visit thereafter. The only criteria for discontinuing the intervention will be hospitalization due to worsening status. All concomitant care and interventions for health reasons are permitted during the trial.

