### Main outcome

#### Physical functional capacity

Improvement in aerobic capacity and resistance, measured by the six-minute walk test [28]

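### The between-arm walk comparison is tied to a t-test that, without imputation, uses only patients with a walk at that visit; the mixed model already planned would serve the intention-to-treat estimate better

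*Protocol article*

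**What the plan says.** The protocol article's Statistical methods section gives each method a role:

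- Between arms: "Between-group differences will be studied using the Student’s t-test for two samples".
- Within an arm: "The effect of the intervention or standard care will be calculated using the Student’s t-test or Mcnemar’s test for paired samples".
- Mixed model: "A mixed linear regression model will be used to evaluate trends in each arm, adjusting for variables of interest".
- Adjustment: "For the inference analysis, co-variables that correlate (sociodemographic factors) will be used and adjusted analyzes made". No model is named for this.
- Analysis sets: "All analyzes will made per protocol and intention-to-treat".

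The main outcome is "Improvement in aerobic capacity and resistance, measured by the six-minute walk test". Table 2 schedules the walk in both arms at two visits only, week 4 and week 23.

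Under Strategies to improve adherence to the protocol, the article states: "The only criteria for discontinuing the intervention will be hospitalization due to worsening status". It does not say that assessments then stop. Of missed visits it says: "If patients do not attend, they will be contacted again to avoid losses".

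The article states neither a complete-case rule nor an imputation rule.

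**The concern.** An intention-to-treat comparison aims to cover all randomised patients in their assigned arms. A two-sample t-test on the data as collected covers only those with a walk at the visit tested. A patient who walked at week 4 and missed week 23 contributes nothing, although the first walk says much about the second. The one planned method that could keep this patient, the mixed model, is worded for a different purpose.

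This matters if missing walks are related to fitness and the loss differs between arms. The patients who remain are then a different selection in each arm, and the estimated difference shifts. If weaker walkers are lost more often from control, the remaining controls look fitter and a real benefit is understated. If they are lost more often from intervention, it is overstated. Even with equal loss, the week-4 information goes unused.

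**Working it through.** **Inputs from the article (Sample size calculation, Table 2).** SD 80 m; difference 30 m; two-sided alpha 0.05; power 80%; 142 per arm; walks at weeks 4 and 23. No loss rate is stated.

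**The plan's own figure.** n per arm = 2(1.96 + 0.84)² × 80² / 30² = 111.6, so 112 (113 with the exact t-test), not 142. An unstated 20% loss (113 / 0.80 = 141.25, so 142) or an SD of 90 m (141.3, so 142) would give 142. That is a separate matter. Here it shows only how much room the t-test has.

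**Power of the t-test under loss unrelated to the walk.** Power ≈ Φ(30/SE − 1.96), with SE = 80√(2/m) and m patients per arm with a walk.

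| Loss | m | SE (m) | Power |
|---|---|---|---|
| 0% | 142 | 9.49 | 88.5% |
| 10% | 127.8 | 10.01 | 85.0% |
| 20% | 113.6 | 10.61 | 80.7% |
| 25% | 106.5 | 10.96 | 78.1% |

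Power stays at 80% or more up to about 20–21% loss (1 − 113/142 = 20.4%; 1 − 112/142 = 21.1%). Up to that level the question is mainly bias.

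**Bias by hand.** Suppose missing patients would have walked g metres less than those observed, in both arms. Each observed mean is then too high by (proportion missing) × g, and the bias of the difference is (p_int − p_ctl) × g. With 15% and 25% missing this is −0.10 × g. For g of 30 to 50 m the bias is −3 to −5 m, so 25 to 27 m is estimated for a true 30 m. With equal proportions it is zero.

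**Simulation (assumed inputs).** 142 per arm, SD 80 m, correlation between the two walks 0.6–0.8, log-odds of loss 0.7–1.0 per SD of a shorter walk, at least 2,500 trials per scenario. The model is the likelihood estimate from both visits.

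| Scenario | t-test | Model using both walks |
|---|---|---|
| 25% control, 15% intervention; loss depends on week-4 walk; true 30 m | about 25–27 m, power 67–73% | about 30 m, power 83–86% |
| Same loss, true effect 0, correlation 0.7 | about −4 m | about 0 m |
| 20% in both arms; true 30 m | about 30 m, power 80–83% | about 30 m, power 82–86% |
| 25% and 15%; loss depends on the week-23 walk itself; true 30 m | 23.5–25.4 m | about 26–28 m |

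In the equal-loss row the gain within a scenario is about 2 points of power; the ranges span repeated runs and correlations.

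A more extreme case lets loss depend on the week-4 walk in one arm only (10% to 20% nominal loss, correlation 0.7). The t-test then gives between 18 and 41 m, depending on which arm, while an estimate using the week-4 walk stays at 30.0 to 30.3 m.

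**The case against.** A reader might infer that the promised intention-to-treat result is in fact a completers-only result. The article does not support that, for three reasons.

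- It sets no complete-case rule. A t-test can follow imputation, and handling of missing data is commonly left to a full protocol or SAP, neither of which is shown.
- It does not make the t-test the sole or primary result. A mixed model and adjusted analyses are also planned.
- Patients who stop the intervention but still walk remain in their assigned arm. Only missing walks are at issue, so the comparison is not a per-protocol one.

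The loss pattern is also open to challenge. The 25% and 15% have no basis in the document. Non-attenders are re-contacted. Under Standard care group, data collection is the same in both arms, and Table 2 gives both the same physician, nurse and cardiologist follow-up. The extra interviews end at week 8, or optionally week 13, at least ten weeks before the final walk. Hospitalisation for worsening stops the intervention, not necessarily the assessment. With greater loss in control, the bias is against the trial's hypothesis.

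Finally, a model built on the week-4 walk is unbiased by construction when loss depends on that walk. If worsening after week 4 drives the loss, it repairs the bias only in part.

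All of this stands and limits the size of the point. It does not remove it. The t-test is the only method the article ties to between-group differences, and the better-suited model is planned but given another role. The conservative direction also holds only if control loses more patients; the reverse pattern would overstate the benefit.

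**Conclusion.** The point holds as a weakness in how the methods are assigned, not as a demonstrated bias. As written, and without imputation, the between-arm test is an available-walks comparison that discards the week-4 walk of patients who miss week 23. The cost ranges from about 2 points of power, with essentially no bias (equal 20% loss), to an understatement of about 3–5 m in a true 30 m with power about 67–73% (25% and 15% loss depending on the week-4 walk). The mixed model recovers about 30 m and 83–86% power in the latter case. If loss depends on the unobserved week-23 walk, it narrows the bias without removing it.

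All these figures rest on assumed loss rates, loss mechanisms and correlations. The article supplies only the SD, the target difference and the arm size. The change is a cheap improvement worth making before analysis.

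**What to change.** In Statistical methods, state that the intention-to-treat between-arm difference in walk distance at week 23 comes from the mixed model already planned. Fit it to all randomised patients with at least one walk, with arm, visit (weeks 4 and 23), arm-by-visit and an unstructured covariance. Table 2 places the week-4 walk after allocation and after the first interviews, so it should enter as an outcome and not as a baseline covariate.

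Keep the two-sample t-test as supportive. Report, by arm and reason, the patients who miss the week-23 walk and those with no walk at all; the latter still drop out of the model, because Table 2 schedules no walk before week 4.

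The cost is wording only, with no new data or patients. The estimate then rests on walks being missing at random given the week-4 walk. This is weaker than what the t-test on available walks needs, but it is still an assumption, so a sensitivity analysis for departures from it is advisable.

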## Discussion

This protocol aims to study the effectiveness of a post-AMI CR program with MI in PHC. CR will be carried out in PHC centers and may be innovative in allowing patients to access CR.

No differences in mortality, reinfarction, revascularization, hospitalization, and exercise between CR at home or in hospitals have been shown [13]. However, there is a lack of programs and research specifying CR programs in PHC, and no indicators have assessed standard care. As no program has been designed specifically in Spain, if the results of this trial are as expected, this PHC-based program could increase participation in CR post-AMI programs. Research on non-hospital-based CR programs has a poor level of methodological reporting, with details of interventions often poorly reported. Therefore, to achieve sufficient quality, we have followed the seven core recommendations of the UK CR standards [35]. The fourth component refers to the assessment of patient needs which, in the PHC context, refers directly to a patient-centered approach. In our CR program, the patient-centered approach and the patient’s self-perceived objectives will be covered by the MI component which, at the same time is the core component of the whole program. Our perspective is that MI rehabilitation will be effective only when placing the patient as the individual at the center of the whole CR program.

### Limitations of the study

The study will be carried out in patients from a single, urban hospital. This may limit the generalizability of the results to semi-urban or rural areas. Second, the complete blinding of participants to their group assignment may not be guaranteed because patients may discover they have been assigned to the control group. However, this issue is common in MI research. Finally, the duration of the follow-up will not allow study of the long-term effects, although a subsequent study with a cohort design is possible. In addition, the proposed study is restricted to the improvement in the first six months of outpatient treatment of CR.

## Data Availability

The study steering committee will accept requests for data sharing once the study is completed. The steering committee will evaluate the scientific soundness of each proposed project and will grant access whenever projects seem scientifically sound. All data sharing will apply to national and international legislation, rules, and other regulations by regional or national authorities. Applications for data require a formal application and will be decided upon by the board of the scientific group.

## Abbreviations

AMI: Acute myocardial infarction
BP: Blood pressure
CR: Cardiac rehabilitation
CRP: Cardiac rehabilitation programs
CVD: Cerebrovascular disease
DM: Diabetes mellitus
HF: Heart failure
LDL: Low-density lipids
MI: Motivational interviewing
PHC: Primary healthcare
RCT: Randomized clinical trial
